Good Psychiatric Management (GPM) is a basic clinical management procedure that distills the fundamentals of how to treat any patient with BPD, starting with psychoeducation about the development, course, and treatment of the disorder and disclosure of the diagnosis (Gunderson & Links, 2014). GPM was shown to be non-inferior to Dialectical Behavior Therapy, a gold-standard specialized treatment for BPD, in a randomized control trial (McMain et al., 2009). Further research has supported psychoeducation as an effective intervention, independent of psychotherapeutic treatment. Zanarini et al. randomized 50 late adolescent women to attend a one day, in-person psychoeducational workshop about BPD in week 1 of the study or to a waitlist control condition. Participants in the workshop condition had significantly greater reductions in impulsivity and storminess of close relationships than participants in the waitlist condition (Zanarini et al., 2008). The same research group assessed the efficacy of a self-guided online psychoeducational program in a randomized control trial of 80 adult women with BPD and found that women in the treatment condition had a significantly greater reduction in all five sectors of borderline symptomatology studied (affective, cognitive, impulsivity, interpersonal, and over-all; Zanarini et al., 2017). Lastly, psychoeducation in a weekly group setting conducted over six sessions was tested against a waitlist control, and participants in the group had significantly greater reductions in affective, interpersonal, and cognitive symptoms, but not impulsivity (Ridolfi et al., 2019).

This study aims to test the feasibility and preliminary efficacy of psychoeducation delivered through a series of pre-recorded videos. Delivering the psychoeducation asynchronously avoids two significant sources of variability in treatment response: the therapist themself and the therapist’s role in the alliance (Wampold et al., 2005; Baldwin et al., 2007). This may be particularly helpful to individuals with BPD, who are hypersensitive in interpersonal relationships and interactions.

Our protocol also includes a rigorous battery of assessments, including neuropsychological testing with or without feedback, ecological momentary assessment (EMA), and traditional self-report measures. In addition to supporting a comprehensive view of participants’ change over time, this battery of assessments may also serve as an auxiliary intervention in itself. The EMA assessments may promote improved self-awareness, which has been shown to be impaired in adults with BPD (Pourmohammad et al., 2021). While there has been limited research regarding feedback on neuropsychological assessments, numerous published case studies have reported the benefits of feedback, which also increases self-awareness and allows support to be focused on areas of more severe impairment, while enhancing areas of higher ability (Finn, 2003; Gass & Brown, 1992; Gorske, 2008; Lopez et al., 2008; Malla et al., 1997). In addition, one non-randomized trial found that receiving feedback on neuropsychological assessment improved patient outcomes on metrics including quality of life and personal mastery (Rosado et al., 2018).

The aims of this study are significant for both patients and clinicians. Many individuals with BPD are unable to access care due to a lack of treatment options in their locale, stigma on the part of providers, or prohibitive costs in treatments not covered by insurance (Iliakis et al., 2019). Similarly, many primary care physicians (PCPs) are unable to provide referrals to appropriate treatment for their patients with BPD for the same reasons. A suite of online psychoeducational videos may augment treatment for a patient who is in a supportive therapy with a generalist clinician, or may be a first step in treatment that can be prescribed by a PCP.

1. **Specific Aims and Objectives**

**Specific Aims**

1. To test the feasibility and efficacy of a suite of 10 online educational videos about BPD as a scalable intervention to reduce BPD symptom severity.
2. To test the feasibility of an online assessment protocol that incorporates standard self-assessment and neuropsychological performance testing.
3. To test the feasibility and efficacy of brief, one-time neuropsychological feedback as an intervention to reduce BPD symptom severity.

**Hypotheses**

1. Participants who receive the suite of educational videos about BPD will have reduced symptom severity post-treatment compared to those who receive a suite of similar control videos without information about BPD.
   1. This effect will be mediated by increased knowledge about BPD.
   2. Differences in symptom severity between the BPD and non-BPD focused video conditions will be associated with measurable differences in self-reported symptoms and neuropsychological performance.
2. Participants who receive feedback will have reduced symptom severity post-treatment compared to those who do not receive feedback.
   1. This effect will be mediated by increases in consistency of self-report and social wisdom (i.e., learning) and decreases in social disconnection.
3. The educational videos and neuropsychological feedback will yield separate, measurable effects on emotional and interpersonal sensitivity in BPD.
4. **General Description of Study Design**

This study will follow a sequential multiple randomization design with two points of division: 1) psychoeducational or control videos, 2) feedback on neuropsychological assessments or no feedback. This yields three participant groups (the control/sham group will not undergo the second randomization):

- Psychoeducational videos x neuropsychological feedback
- Psychoeducational videos x no feedback
- Control/sham videos x no feedback

**Study Schema
[figure not shown]
**

1. **Subject Selection**

**Inclusion Criteria:**

- Reliable access to a smartphone with a data plan for the duration of the study.
- Ability to speak and understand English.
- Age 18 years or older.
- Diagnosis of BPD within the past 6 months.
- Awake and able to complete EMA surveys between 9am-9pm on most days.
- Located within Massachusetts

**Exclusion Criteria:**

- Cognitive disability that impedes ability to participate in the study.
- Current psychiatric symptoms that interfere with the individual’s ability to provide consent or complete the research procedures (e.g., acute mania, acute psychosis, or eating disorders threatening medical stability).

**Recruitment Procedures:**

- The study coordinator (research assistant) is responsible for identifying and recruiting individuals.
- Individuals will be recruited on a rolling basis between April 2023 - May 2024, or until we reach our goal of 100 participants.
- Participants will be recruited in several ways. We will do some of the recruitment from units within McLean through designated research and clinical teams on the units. Potential participants meeting inclusion and exclusion criteria will be identified by embedded research assistants in the units and through Epic chart reviews by the study research assistant and PI. For participants identified through Epic, the study research assistant will contact the unit embedded RA and treatment team to ensure it is clinically appropriate to approach the patient for research. A unit staff member will ask the patient if they are interested in speaking with research staff. Capacity to consent or documentation of discussion of clinical appropriateness forms will be completed for all inpatients recruited.
- For the Behavioral Health Partial (BHP) program, treatment teams will obtain permission from patients to be contacted via email about a research study. BHP staff will then notify patients of the opportunity to participate in this research study via email (email template submitted to the IRB). Interested potential participants from the BHP will be the one to initiate contact with study staff. Study staff will then correspond with participants to set up a screening meeting.
- Study information will also be posted to the Mass General Brigham Rally platform and credible advocacy websites including the National Education Alliance for BPD in the form of a virtual flyer/post advertising the details of the study, a link to the virtual eligibility screening survey (see **Screening Questionnaire**), and the contact information of the study team (see **Advertisements**).
- Study information will be advertised with physical flyers posted in MGB-affiliated hospitals, as well as non-MGB hospitals including Boston Medical Center, UMass Memorial Medical Center, Beth Israel Deaconess Medical Center, Massachusetts Mental Health Center, UMass Amherst, Cambridge Health Alliance, and Tufts Medical Center.
- By advertising on the internet and in general healthcare settings to recently diagnosed individuals, we hope to mitigate the bias created by recruiting from subject pools who are already receiving specialized treatment, which is generally difficult to access (Iliakis et al., 2019).
- At branching points in the design, we will use block randomization to balance demographic and baseline variables between groups. Specifically, we will balance gender and BPD symptom severity at each randomization point.

1. **Subject Enrollment**

Participants will complete an online survey hosted on REDCap to determine their eligibility based on our inclusion and exclusion criteria. Eligible participants will be asked to meet with the PI or research assistant for a virtual consent discussion and will then sign a consent form.

Once enrolled in the study, all participants will fill out the baseline assessment battery, including demographic questions, the BPD Knowledge Test, Borderline Symptom List-23 (BSL-23), Patient Health Questionnaire-9 (PHQ-9), McLean Assessment of Rejection Sensitivity (MARS), Three-Item Loneliness Scale (LS-3), and the Level of Personality Functioning Scale - Brief (LPFS). They will then be randomized to receive the psychoeducational videos or the control videos using block randomization, considering demographic factors and baseline BPD symptoms (BSL-23). The randomization will be weighted such that 2/3 of participants (anticipated N=67) are in the BPD video condition and 1/3 (anticipated N=33) are in the non-BPD video condition. After completion of the first phase of the study, participants in the BPD psychoeducation arm will be randomly assigned to receive feedback or not. The second randomization will divide the participants equally, with an anticipated N=33 (or 34) in each arm.

1. **STUDY PROCEDURES**

**Outcomes:** The primary outcomes are borderline symptom severity (i.e., score on the Borderline Symptom Checklist) after each intervention point (timepoints B and C) and at the follow-up (timepoint D). The secondary outcomes are depressive symptoms severity (i.e., score on the Patient Health Questionnaire) after each intervention point (timepoints B and C) and at the follow-up (timepoint D).

**Screening**

Subjects will complete an online survey hosted on REDCap that includes a series of questions about their location, current psychiatric symptoms, availability, and smart phone access in order to assess their eligibility.

**Consenting**

After screening and before the first research assessment, eligible participants will complete the informed consent process. At the end of the screening survey, eligible participants will be asked to provide their contact information. The study staff will contact eligible participants to schedule a virtual consent discussion. The consent discussion will take place on an MGB Zoom account, and the Zoom link and consent form will be emailed to the participant in advance using secure MGB email. When participants present for the virtual consent discussion, the PI or study research assistant will fully explain the purpose of the research, the study procedures, the risks, discomforts, and possible benefits, and alternative existing treatments for BPD. The PI or research assistant will answer any questions from the participant. All participants in this study must be judged capable of understanding the nature of the study as well as the discomforts and potential benefits. The participants will be asked to return the signed consent form within 48 hours if they would like to participate, and the form will be signed by the PI or research assistant who completed the consent discussion. A fully signed copy of their consent form will be returned to the participant via secure email.

**Baseline Assessment (Timepoint A) - Day 1 (55 minutes)**

The baseline assessment battery includes a demographic questionnaire, neurocognitive tests, and self-report questionnaires regarding mental health and social functioning. The total length of the assessment is approximately 55 minutes.

- *Demographic Questionnaire:* Questions delivered through REDCap regarding participants’ sociodemographic information.
- *Self-Report Questionnaires:* These surveys are hosted on REDCap and will take about 25 minutes. The questionnaires are listed below.
- *Cognitive Tests:* Tests are hosted and administered on the digital research platform TestMyBrain.org. Participants will be automatically re-directed to TestMyBrain.org after completing the REDCap portion of the assessments. These tests take about 30 minutes in total. The measures are listed below, along with the self-report questionnaires.

Baseline Self-Reports and Cognitive Tests

**Self-Reports**

1. Treatment History Questionnaire (5 minutes)
   1. This questionnaire is adapted from the Background Information Schedule (*Zanarini MC: Background Information Schedule. Belmont, Mass, McLean Hospital, 1992*) It asks about the participant’s experiences with past forms of psychotherapy and pharmacological treatment.
2. BPD Knowledge Test (4 minutes)
   1. This questionnaire, developed for the study, assesses the participant’s knowledge about symptoms, basic facts, long term course, comorbidities, and treatment of BPD. There is no existing measure of BPD knowledge.
3. Borderline Symptom List (BSL-23) (4 minutes)
   2. This questionnaire assesses the severity of BPD symptoms.
4. Patient Health Questionnaire (PHQ-9) (2 minutes)
   2. This questionnaire assesses depression symptoms.
5. McLean Assessment of Rejection Sensitivity (MARS) (2 minutes)
   1. This unpublished questionnaire assesses trait-level rejection sensitivity.
6. Three-Item Loneliness Scale (LS-3) (1 minute)
   2. This questionnaire assesses the level of overall loneliness.
7. San Diego Wisdom Scale (SD-WISE) (5 minutes)
   2. This questionnaire assesses general wisdom.
8. Level of Personality Functioning Scale-Brief (LPFS) (4 minutes)
   2. This questionnaire assesses traits of personality disorders dimensionally, rather than diagnostically or categorically.

**Cognitive Tests**

1. Gradual Onset Continuous Performance Test (CPT) (6-minute average completion time)
   1. Participants see a series of city or mountain scenes. The participant is asked to press a button whenever they see a city scene and withhold a response whenever they see a mountain scene. This a test of sustained attention and response inhibition. https://testmybrain.org/tests/gradCPT/index_down_mobilized.php
2. Reading the Mind in the Eyes (RMET) (8-minute average completion time)
   1. Participants see a series of images showing only the eye region of someone’s face. The participant is asked to choose which of four complex emotion words describes the mental state of the person depicted in the image. This is a test of theory of mind and social understanding. https://www.testmybrain.org/tests/mind_in_eyes/
3. Belmont Emotion Sensitivity Test (BEST) (7.5-minute average completion time)
   1. Participants see a series of pairs of faces and are asked to indicate which one is expressing more of the target emotion (happiness, anger, or fear). This test measures face emotion perception. https://www.testmybrain.org/tests/emotion_comparison/anger.html
4. Digit Span Tests - Forward and Backward (DST) (7-minute average completion time)
   1. Participants are asked to recall sequences of digits of increasing length, either in the same order as presented (Forward condition) or in the opposite order (Backward condition). This test measures auditory span, short term memory, attention, and working memory (backward version). This test will be presented to participants in a similar format to the other cognitive tests, linked above. A demo link is not currently available for this test.
5. Digit Symbol Matching Test (DSMT) (2-minute average completion time)
   1. Participants are asked to use a symbol-number key shown on screen to match as many symbols and numbers as possible in 90 seconds. This test measures processing speed and visual short-term memory. This test will be presented to participants in a similar format to the other cognitive tests above.

**Ecological Momentary Assessment - Days 1-30 (6 minutes per day)**

EMA data will be collected over the course of 30 days. Participants will complete one assessment each day at a randomly generated time between the hours of 9:00am-9:00pm. The assessment will be delivered to the participant’s smart phone as a text alert. The text message will contain a link to a REDCap survey, which will then re-direct to TestMyBrain.org for completion of two brief cognitive tests (the brief version of the Gradual Onset Continuous Performance Test - 1-2 minutes and the Digit Symbol Matching Test – 1-2 minutes) and questions regarding the participant’s immediate surroundings, functioning, recent social interactions, as well as feelings of connectedness, threat, aloneness, and despair. For the full text of the EMA questions, see the **EMA** document.

EMA survey data will be collected through REDCap and stored in the secure REDCap database. The EMA cognitive test data will be collected through TestMyBrain.org and stored in the secure TestMyBrain database (see **Risks and Discomforts**). The cognitive tests and EMA questions will not be linked to any identifying participant information. Instead, the survey links will be unique to each participant and individualized with a coded ID. IP addresses will not be stored with the data, and after the cognitive test data has been downloaded from the TestMyBrain database, any study-specific information will be deleted from the database.

The text messages including the EMA survey links will be sent using REDCap and Twilio. Twilio is a cloud computing platform that enables text messaging from a website. The phone numbers, and any other patient health information, will not be stored in REDCap and will not be permanently stored in Twilio.

**Second Assessment (Timepoint B) - Day 15 (35 minutes)**

The second assessment battery includes repeat administrations of one neurocognitive test, and some self-report questionnaires regarding mental health and social functioning that were administered at baseline. The protocol for administering the tests and questionnaires is the same as at baseline.

1. DST
2. BPD Knowledge Test
3. BSL-23
4. PHQ-9
5. LS-3
6. LPFS
7. CSQ-8
   2. This questionnaire is a brief acceptability measure.
8. Hospitalization Check-In
   1. This brief, unpublished questionnaire assesses if the participant has visited the emergency department, been hospitalized, or started a residential treatment program since the previous time point.

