**Third Assessment (Timepoint C) - Day 30 (30 minutes)**

The third assessment battery includes repeat administrations of some neurocognitive tests, and some self-report questionnaires regarding mental health and social functioning that were administered at baseline. The protocol for administering the tests and questionnaires is the same as at baseline.

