1. CPT
2. DST
3. DSMT
4. BSL-23
5. PHQ-9
6. LS-3
7. LPFS
8. Hospitalization Check-In

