**Follow-up Assessment (Timepoint D) - Day 60 (50 minutes)**

The fourth assessment battery includes repeat administrations of all neurocognitive tests and self-report questionnaires regarding mental health and social functioning that were administered at baseline. The protocol for administering the tests and questionnaires is the same as at baseline.

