8. BSL-23
9. PHQ-9
10. MARS
11. LS-3
12. SD-WISE
13. LPFS

**Schedule of Assessments**

| **Measure** | **Baseline (Time 1)**  **Day 1** | **Time 2**  **Day 15** | **Time 3**  **Day 30** | **Follow-up**  **Day 60** |
| --- | --- | --- | --- | --- |
| **Demographics** | X |  |  |  |
| **CPT** | X |  | X | X |
| **RMET** | X |  |  | X |
| **BEST** | X |  |  | X |
| **DST** | X | X | X | X |
| **DSMT** | X |  | X | X |
| **Treatment Hist.** | X |  |  | X |
| **BPD Knowledge** | X | X |  | X |
| **Hosp. Check-In** |  | X | X |  |
| **BSL-23** | X | X | X | X |
| **PHQ-9** | X | X | X | X |
| **MARS** | X |  |  | X |
| **LS-3** | X | X | X | X |
| **SD-WISE** | X |  |  | X |
| **LPFS** | X | X | X | X |
| **CSQ-8** |  | X |  |  |
| **EMA Measures** | *Daily from Day 1 - Day 30* | |  |  |

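### The Hospitalization Check-In is not scheduled at Day 60, so no described measure systematically asks about ED visits, admissions or residential treatment between Days 30 and 60

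*Protocol*

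**What the plan says.** The Hospitalization Check-In is introduced as item 8 of the Second Assessment (Timepoint B, Day 15). It is a brief unpublished form that "assesses if the participant has visited the emergency department, been hospitalized, or started a residential treatment program since the previous time point". It appears again at Day 30, as "8. Hospitalization Check-In" in the Third Assessment list. The thirteen-item list under Follow-up Assessment (Timepoint D, Day 60) does not include it. In the Schedule of Assessments the row reads "Hosp. Check-In | | X | X", with the baseline and Day 60 cells empty.

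The Protocol gives a rule for the Day 60 battery: it "includes repeat administrations of all neurocognitive tests and self-report questionnaires regarding mental health and social functioning that were administered at baseline". The Check-In was not a baseline measure, so the rule leaves it out. No other reason is given.

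Under Study Procedures, BSL-23 at Timepoint D is among the primary outcomes and PHQ-9 at Timepoint D is among the secondary outcomes.

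**The concern.** A form that looks back only to the preceding visit covers the whole study only if it is given at every later visit. Here it stops at the visit before last, and the interval left open is the longest of the three.

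Two things are at stake. The first is interpretation of the Day 60 comparison. An inpatient or residential stay between Days 30 and 60 is intensive care outside the study, and it could move a BSL-23 or PHQ-9 score taken at the end of that interval. With about 33 participants per arm, a few such stays falling unevenly could matter, and the study would have no systematic record of them. The second is description. Recruitment includes inpatient units and a partial hospital program, so acute-care use is plausible in this sample. Counts by arm over the full period would help plan the larger trial for which this pilot is meant to prepare.

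The gap lies in what is collected, so no later analysis plan can repair it.

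**Working it through.** The Protocol states no figure on this point to reproduce. The check compares the visit lists with the schedule, works out the intervals, and looks for other sources.

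**1. Lists against table.**

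| Visit | Item list | Schedule of Assessments |
|---|---|---|
| A, Day 1 | Check-In absent | empty |
| B, Day 15 | item 8 | X |
| C, Day 30 | item 8 | X |
| D, Day 60 | absent | empty |

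Lists and table agree at every visit, so the omission is not an effect of a broken table.

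**2. Intervals covered** (visit days from the section headings).

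- Check-In at Day 15 reaches back to Day 1: 15 − 1 = 14 days.
- Check-In at Day 30 reaches back to Day 15: 30 − 15 = 15 days.
- Day 30 to Day 60: 60 − 30 = 30 days, with no Check-In.
- Total elapsed: 60 − 1 = 59 days.
- Covered: (14 + 15)/59 = 29/59 = 49%.
- Uncovered: 30/59 = 51%. Counted from Day 0 it is 30/60 = 50%.

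**3. Other sources for Days 30 to 60.**

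- *Treatment History Questionnaire* (given at baseline and Day 60). The baseline Self-Reports section describes it as asking about earlier psychotherapy and medication. ED visits, admissions and residential care are not mentioned, and no look-back period is stated. Its items are not shown.
- *EMA.* It runs for 30 days and ends on Day 30.
- *Adverse events* (Monitoring and Quality Assurance). Events are to be documented and reported under the IRB policy, and monitoring is continuous. No scheduled question to participants is described.
- *Participant contact* (Risks and Discomforts). The described steps begin when a participant contacts staff.

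None of these, as described, puts the Check-In's questions to every participant for Days 30 to 60.

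**4. After the change.** With the same wording at Day 60, the windows become 14 + 15 + 30 = 59 of 59 days (100%).

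**The case against.** The best defence is that the Treatment History Questionnaire and the Check-In sit at exactly complementary visits: the first at baseline and Day 60, the second at Days 15 and 30. That pattern fits a plan in which the short form stands in where the longer one is not given. The longer form is adapted from an existing schedule and its items are not shown, so it may record a residential stay or an admission. This stands as a possibility, and it is why the fix offers an alternative. It does not close the gap, because the Protocol's description names neither these events nor a period since Day 30.

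It is also fair to say that the omission is not an internal contradiction, since lists, table and the Day 60 rule are consistent. Hospitalization is not a named outcome, appears in no hypothesis and is used in no listed analysis. The study is an exploratory pilot that the Protocol itself describes as underpowered. These points limit the consequence but do not remove it.

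A reader might infer more than the document supports:

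- *That about half of all acute-care events are missed.* This needs a constant event rate, and the Protocol gives no rate. Because some participants come from inpatient or partial hospital care, a constant rate is doubtful.
- *That two thirds of the time after feedback is unobserved (30 of 45 days).* This assumes feedback is sent on Day 15. The Protocol gives no send date, only that feedback belongs to the second phase.
- *That harms are counted for only half the study.* The Check-In is never called a safety measure, BSL-23 and PHQ-9 are collected at Day 60, and adverse-event monitoring runs throughout.
- *That co-treatment cannot be examined at Day 60 at all.* Psychotherapy and medication fall within the description of the Treatment History Questionnaire given at that visit.

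**Conclusion.** The point holds as a gap in data capture. As described, no measure systematically asks about ED visits, hospitalization or starting residential treatment during Days 30 to 60. That is 30 of 59 elapsed days, directly before the Day 60 primary and secondary outcomes. Some events may be caught through the Treatment History Questionnaire or adverse-event reports.

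The conclusion assumes that the Check-In is used as worded and that the Treatment History Questionnaire asks only what its description says. If its Day 60 items do ask about these events since Day 30, what remains is a matter of documentation.

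The number of events affected cannot be estimated from the Protocol. The effect is on describing acute-care use and interpreting the Day 60 comparison. The change is worth making because it costs little and the information cannot be recovered afterwards.

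**What to change.** Add the Hospitalization Check-In to Timepoint D, both in the Follow-up Assessment item list and in the Day 60 cell of the Schedule of Assessments. If the Day 60 Treatment History Questionnaire already asks about ED visits, admissions and residential treatment since Day 30, say so in its description and use those items instead.

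Report these events descriptively by arm over Days 1 to 60. Keep all randomized participants in the Day 60 BSL-23 comparison. Rerunning that comparison without participants admitted since Day 30 is not recommended: admission occurs after randomization and may itself be affected by the intervention, so excluding on it breaks the randomized comparison.

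Cost: a few extra questions on an existing brief form at an existing visit, and a minor amendment.
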